# Cluster-randomized trial of Homework, Organization, and Planning Skills program compared to treatment as usual/waitlist for youth ages 11–14: Study protocol for conceptual replication

**DOI:** 10.1371/journal.pone.0343894

**Published:** 2026-06-11

## Abstract

**Background:**

Organization, time management, and planning (OTMP) difficulties are associated with academic underachievement. OTMP skills training programs are effective in reducing OTMP deficits and improving academic performance. A randomized controlled trial of Homework, Organization, and Planning Skills (HOPS) for students ages 11–14 found it to be effective with medium to large effects. In that study, HOPS was provided by counselors employed by the research team. This study is a replication examining HOPS under more authentic conditions when providers are employed by schools serving enrolled students. The primary aim is to evaluate HOPS offered by school providers in relation to treatment-as-usual/waitlist (TAU/WL). To respond to limited school resources post-COVID-19, HOPS is also provided by research team members, creating the opportunity to replicate the findings from the prior trial and explore differential effectiveness when HOPS is implemented by school vs. research providers.

**Methods:**

Students in about 30 schools serving students ages 11–14 will be enrolled. Schools are randomly assigned to HOPS vs. TAU/WL on a 2:1 ratio. Students assigned to HOPS schools are randomly assigned to a school vs. research provider on a 1:1 basis. Providers receive two hours of training and additional assistance on request. Child outcomes related to OTMP skills, homework, and academic performance are assessed at post-treatment, 6-month (from baseline) follow-up, and 12-month follow-up. HOPS sessions are video recorded for fidelity coding. Potential effect modifiers include student ADHD, oppositional defiant, and internalizing symptoms, and family socioeconomic level. Analyses will use mixed effects modeling. The goal of the study is to enroll 135 participants, yielding a minimal detectable effect size of 0.50, within the expected range based on prior research.

**Discussion:**

The study is unique in examining intervention implementation and effectiveness when intervention is provided under authentic practice conditions.

**Trial registration:**

This study was registered with clinicaltrials.gov (NCT04465708).

## Introduction

Among the many factors that influence academic performance, executive functioning (EF) deficits are key predictors [1]. Organization, time management, and planning (OTMP) skills are aspects of EF that are particularly associated with students’ academic performance [2]. Organizational demands increase over the course of schooling and are highly salient during the middle school grades.

Given that OTMP skills are predictive of later academic achievement, schools need effective interventions to support students with deficits in these areas [2,3]. Several intervention programs targeting OTMP skills have been developed and shown to be effective [4,5–8]. For the middle school population (ages 11–14), the Homework, Organization, and Planning Skills (HOPS) program has been shown to be effective and feasible to implement. HOPS is a 16-session child skills training program that provides training to middle school students in school materials organization, homework management, task planning, and time management. HOPS was designed to be provided in 20-minute sessions on an individualized basis, although it can be implemented with a small group of students [9]. In addition, HOPS includes parent consultation and often teacher consultation to promote generalization of newly acquired skills in real-world settings.

### Prior research on HOPS program

In an early study of HOPS, the program was implemented by school mental health professionals in participating schools to 47 students identified as having ADHD and academic problems [10]. The study showed that school counselors demonstrated a high level of fidelity to intervention content. In comparison to a treatment-as-usual, waitlist (TAU/WL) control condition, caregivers in HOPS reported their children made significant improvements in organized actions (Cohen’s *d* = 0.88), task planning (*d* = 1.05), and homework completion behaviors (*d* = 0.85). Outcomes based on teacher ratings did not show improvement. Gains based on caregiver ratings generally were maintained at 3-month follow-up. In addition, HOPS participants demonstrated a superior grade point average (GPA) in comparison to TAU/WL.

HOPS was evaluated subsequently in a large-scale randomized controlled trial (RCT, *n* = 280, 7 schools; [4]). The trial was conducted in authentic practice settings (schools). Intervention providers were school counselors who had recently graduated, but they were hired and supervised by the research team. The findings revealed that, compared to TAU/WL, students receiving HOPS demonstrated significant improvements with large effect sizes in caregiver ratings of homework performance (*d* = 1.29), task planning (*d* = .79), materials management (*d* = .81), and organized actions (*d* = 1.14). Improvements based on teacher ratings were significant with medium effect sizes in materials management (*d* = .53) and organized actions (*d* = .55). Findings showed evidence of sustained effects when assessed about 3 months after intervention. An examination of implementation factors revealed that counselor-reported working alliance was a significant predictor of favorable effects of HOPS on outcomes [11].

### Gaps in research on HOPS program

Although the HOPS program was designed primarily for students with ADHD, it has the potential to be effective for students with OTMP deficits who do not have this disorder [9]. Indeed, HOPS may be more useful to school professionals if it can be provided to the broader population of students with OTMP problems, not just those with ADHD [8]. Deficits in OTMP skills are highly common among students with ADHD [12], and they also occur among students with autism spectrum disorder [13], learning disabilities [14], and adverse psychosocial childhood experiences [15]. As such, this study will include students in general education classrooms demonstrating OTMP deficits that may be impacting their academic functioning, regardless of diagnostic status.

HOPS is unique among psychosocial interventions in that it was developed in partnership with schools with a focus on provider usability and feasibility of implementation. However, the manner in which HOPS was applied in the large-scale RCT differs in some important ways from how it likely is applied in routine practice conditions. When schools make the choice to implement HOPS, they need to make use of existing resources. For example, school administrators need to identify one or more school staff to provide the intervention to students. Research is needed to inform school administrators about whether HOPS works in routine practice when the program is offered by school staff. In the original design of the current study, the plan was for HOPS to be provided solely by school professionals working in the school. Because the initial years of this study were implemented during the COVID-19 pandemic, which placed limits on the capacity of schools to participate in this trial, the study design was modified in response to input from school professionals and funding sponsors so that HOPS will be provided by both school professionals (school team providers) as well as educational professionals contracted by the research team who do not work in the schools (research team providers). This shift in design affords the opportunity to test the effectiveness of HOPS when delivered under conditions similar to the original trial (i.e., implementation by members of the research team, [4] as well as conditions more similar to actual practice (i.e., implementation by school providers).

### Importance of intervention implementation and relational processes

Intervention effectiveness depends to a substantial extent on how well the intervention is implemented (provider fidelity) and the extent to which participants are engaged or involved in the intervention [16,17]. Provider fidelity refers to adherence to the steps of the intervention curriculum as well as level of competence in providing intervention. Participant engagement includes attendance, active participation in sessions, and adherence to recommended intervention practices [16]. Another important implementation factor is the working alliance between the provider and student, or the ability of the provider to work with the student in a responsive, collaborative manner [18]. Monitoring implementation processes (provider fidelity, student and parent engagement) and assessing working alliance are especially important when interventions are provided under routine practice conditions, because there is less control over provider fidelity and often less emphasis on promoting intervention in a replicable, standardized manner. In this study, our team will carefully examine provider fidelity, student and parent engagement, and working alliance between the intervention provider and student participants and evaluate the extent to which these factors are associated with improvements in student outcomes.

### Conceptual framework of HOPS

The HOPS program is based primarily on principles of behavior therapy and incorporates elements of cognitive behavioral therapy. Behavioral strategies include verbal instruction, prompting skill use, shaping, and contingency management (with an emphasis on positive reinforcement for effort and performance of targeted OTMP behaviors). HOPS includes parent consultation, and often teacher consultation, to foster generalization of skills across settings and maintenance of strategy use after the intervention has ended. In addition, cognitive-behavioral strategies are used to identify and modify negative, defeatist attitudes that prevent the child from making progress [9].

Several factors, including provider intervention fidelity, as well as student and caregiver engagement in HOPS likely contribute to changes in students’ OTMP skills and homework performance (proximal outcomes). In turn, based on previous research [19,20] changes in OTMP skills likely lead to improved academic (distal) outcomes. Based on research from the previous evaluation of HOPS [4], we expect that severity of student organization problems, ADHD symptoms, and oppositional defiant behaviors at baseline will moderate the effect of intervention on OTMP skills and homework performance. In addition, based on prior research on child organizational skills training at the elementary level, we expected severity of child internalizing symptoms (anxiety and depression) baseline will moderate the effect of intervention [20]. We will also examine whether child medication status (i.e., taking or not taking medication to treat ADHD) and family socioeconomic status modify the effect of intervention. (See Fig 1 for the Spirit Checklist and Fig 2 for the HOPS theory of change.)

**Fig 1 pone.0343894.g001:**
[figure not shown]
Participant timeline: SPIRIT schedule of enrollment, interventions, and assessments. ^a^ -t_1_ = screening, 0 = baseline, *t*_*1*_ = post-intervention, *t*_*2*_ ***=*** 6-month follow up, *t*_*3*_ = 12-month follow up. ^b^ HOPS refers to the Homework, Organization, and Planning Skills program. ^c^ Provider refers to school and research provider unless otherwise indicated (e.g., school or research provider). ^d^ Arrows indicate continuous delivery of HOPS intervention or fidelity/engagement/cost data collection for each HOPS session. ^e^ For students in the TAU/WL condition, fidelity, engagement, and cost data are collected when they receive the intervention (after post-intervention data collection).

**Fig 2 pone.0343894.g002:**
[figure not shown]
HOPS study theory of change. The figure depicts HOPS intervention components and factors that may impact the effect of HOPS on proximal and distal outcomes. OTMP = organization, time management, and planning skills; ODD = oppositional/defiant behavior; SES = socioeconomic status.

### Study purpose and aims

The purpose of this study is to conduct a replication (i.e., replication with design elements that differ from the original trial) of a randomized controlled trial that showed the HOPS intervention provided by counselors employed by the research team improved organizational, time management, and planning (OTMP) skills for middle school students diagnosed with ADHD in relation to students on a waitlist receiving treatment-as-usual (TAU/WL; [4]). The trial will be conducted by an independent research team; the developer, [name], and his team will provide training, technical assistance and follow-up consultation on request to HOPS providers but will not be involved in any intervention evaluation activities. Similarly, the research team evaluating the intervention will not be involved in training or supervising HOPS intervention implementation. The study will test whether HOPS compared to TAU/WL yields similar benefits when implemented by providers on the research team (HOPS-Research Team; HOPS-RT) and school-based professionals (HOPS-School Team; HOPS-ST) for the full range of students who have OTMP skills deficits, not only those with a formal diagnosis of ADHD. The study will examine six aims:

**Aim 1:** Evaluate the difference between HOPS-ST and TAU-WL on improvement in proximal outcomes (organization skills, homework performance) and distal outcomes (academic performance) at post-treatment (4-months after baseline) and explore the intervention’s sustainability (6 and 12-months after baseline). This aim will enable our team to determine the effectiveness of HOPS when provided by school professionals. We hypothesize that students in the HOPS-ST group will demonstrate significantly fewer OTMP skills deficits and homework problems and will show significantly better academic performance at post-treatment compared to students in TAU-WL. In addition, we expect the benefits of HOPS-ST to be maintained at follow-up.**Aim 2:** Examine the effectiveness of HOPS-RT in relation to TAU-WL. This aim will enable our team to replicate the findings of the [name] et al. [4] trial. We hypothesize that students in the HOPS-RT group will demonstrate significantly fewer OTMP skills deficits and homework problems and would show significantly better academic performance at post-treatment compared to students in TAU-WL. In addition, we expect the benefits of HOPS-ST to be maintained at follow-up.**Aim 3:** Explore differences in effect for HOPS-ST and HOPS-RT at post-treatment and follow-up.**Aim 4:** Explore mechanisms of action, specifically whether improvements in OTMP skills and homework performance mediate the effect of HOPS on improvements in academic performance.**Aim 5:** Explore whether student grade level, severity of organization problems, severity of ADHD, oppositional defiant behavior, and internalizing symptoms, and student medication status at baseline moderate the effect of HOPS on outcomes.**Aim 6:** Explore the extent to which treatment fidelity, student engagement, parent engagement, teacher engagement, and provider-student working alliance predicts outcomes for students in HOPS.**Aim 7:** Estimate the cost of providing HOPS under authentic practice conditions in schools.

## Materials and methods

### Trial design

#### Random assignment to study conditions and providers.

The study is a two-group, parallel randomized controlled trial that is designed to include about 30 schools. Random assignment will be conducted at the level of schools and will occur after the school grants approval and the school provider offers consent. The study has two arms: HOPS and TAU-WL. Schools will be stratified by subsidized lunch status (low, medium, high) and randomly assigned to HOPS or TAU-WL at a 2:1 ratio. The sequence of assignments to treatment conditions will be determined using a computer-generated list of random identification numbers, conducted by the study statistician to ensure an unbiased and unpredictable assignment of participants to the study arms. The list of random numbers is generated using the statistical software program R [21]. The study team will inform the principal and school provider after random assignment of the school to study condition has been made. The study is designed to compare HOPS to what students typically receive to address their OTMP skills deficits. A WL design was chosen to be responsive to feedback from school officials who expressed concerns about participating in the study if identified students were not able to obtain HOPS. Students in TAU/WL schools will receive HOPS later in the school year of enrollment or in the school year following the year of enrollment. Students enrolled in the highest grade level in the school (e.g., 8^th^ grade) will be enrolled in the first few months of the school year, so that there is enough time for them to receive HOPS before the end of the school year if their school is assigned to the TAU/WL condition. Students will be enrolled in this study during the period from 25/10/2021–28/02/2026.

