#### Random assignment of students in HOPS schools to school or research provider.

Students randomly assigned to the HOPS condition will be randomized once again to receive HOPS from either a school provider or research provider (on a 1:1 basis). The sequence of assignment of students in the HOPS condition to the school or research provider will be determined by a separate computer-generated list of random identification numbers overseen by the team statistician. Caregivers and teachers will be informed about study assignment after caregiver consent and child assent is provided.

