#### Concealment.

Given that the study is a pragmatic trial being conducted under real-world conditions, no attempt will be made to conceal treatment assignment from caregivers, students, teachers, and intervention providers. In addition, study team members will be fully aware of treatment assignment.

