### Recruitment

Two primary methods will be used to recruit schools. First, emails will be sent to the principals of schools serving students in grades 6–8 located in the large metropolitan area in which the study will be conducted. The selection of schools will be inclusive of districts across the region to achieve balance across subsidized lunch rate levels of the schools (low [0%−30%], middle [31%−60%], and high [61%−100%]). In addition, there will be an intentional effort to recruit schools in urban, suburban, and rural areas. Second, emails will be sent to principals of schools from districts in which we have previously conducted research or those referred to us by school administrators or other researchers. Approval will be obtained from the school principal, school superintendent, and school board (as necessary) prior to conducting research in the school. In addition, principals will be asked to identify one or more school providers to implement the HOPS intervention. School provider(s) must provide consent to participate in the study for the school to be enrolled in the study. Once all approvals and consents are obtained from school professionals, the school will be randomly assigned to a study condition (HOPS vs. TAU/WL).

Students will be referred to the study by their classroom (general education) teachers. School principals will identify the specific strategies to be used in convening teachers, informing them about the study, and obtaining referrals. Teachers will be informed that referral of a student to the study indicates their willingness to complete forms for outcome evaluation. The pool of teachers selected for inclusion in the referral process will be asked to nominate students from their general education classroom: (a) who are struggling the most with OTMP skills, (b) whose OTMP skill deficits interfere with their academic performance, and (c) who have at least one caregiver who speaks English. Each teacher who agrees to participate will complete a nomination form for each referred student for the purpose of determining student eligibility.

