After a student is referred and determined to be eligible, a professional from the school, typically the school provider, will attempt to contact the parent or legal guardian to explain the study, indicate their child has been referred for HOPS through the study, and determine if the family is willing to be contacted by the study team. The school professional will often send a letter to the parent/guardian that includes a link to an electronic survey to offer permission for the study team to contact the family and provide contact information. The school provider may also contact (phone or email) parent(s)/guardian(s) of identified students to introduce the study. When the school gets permission from a family to share contact information with the study team, they will pass that information to the study team. With caregiver approval, a member of the study team will contact the family to determine interest, obtain caregiver consent, and obtain student assent.

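### Students are recruited after their school is randomised, by people who know or may know the arm, so enrolment can differ between HOPS and TAU/WL.

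*Protocol article*

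**What the plan says.** **Timing of randomisation.** The protocol article, under random assignment to study conditions, states: "Random assignment will be conducted at the level of schools and will occur after the school grants approval and the school provider offers consent". The Recruitment section gives the same trigger and then goes on to student referral.

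**Who is told.** For the school: "The study team will inform the principal and school provider after random assignment of the school to study condition has been made". For the research team, the Concealment section adds: "In addition, study team members will be fully aware of treatment assignment".

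**Who recruits.** On referral: "School principals will identify the specific strategies to be used in convening teachers, informing them about the study, and obtaining referrals". General education teachers then nominate. On first contact with families: "After a student is referred and determined to be eligible, a professional from the school, typically the school provider, will attempt to contact the parent". With the family's permission, a study team member obtains consent and assent.

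**Safeguard.** The section on assigning students to providers says: "Caregivers and teachers will be informed about study assignment after caregiver consent and child assent is provided". The Concealment section says no attempt is made to hide assignment from caregivers, students, teachers or providers.

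**Analysis.** Under Data collection and management, variables that differ significantly between groups at baseline become covariates. The Aims 1–3 section plans a multilevel model with student- and school-level covariates, fitted to all children with baseline data.

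**The concern.** Randomising schools makes the schools comparable. It does not make the students comparable if they are chosen, approached or persuaded after the arm is known. The Trial design section credits the random list with unpredictable assignment of participants. That holds for schools only: once a school's arm is known, so is the HOPS or TAU/WL status of every student later recruited there.

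A school provider or consenting staff member who knows the arm may pursue some families harder than others, or describe the study differently. Motivation and family engagement are plausible routes, and neither is fully captured by the measured baseline scores. Both hypothesis-testing contrasts, HOPS-ST vs TAU/WL and HOPS-RT vs TAU/WL, are exposed. HOPS-ST vs HOPS-RT is not exposed in the same way, because those students are individually randomised within HOPS schools.

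**Working it through.** No figure in the plan measures this risk, so the main check is the sequence of steps. Two calculations then show what the planned analysis could and could not catch.

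**1. Sequence**

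| Step | Who acts | Knows the arm? |
|---|---|---|
| School approval, provider consent | School | Not yet assigned |
| School randomised | Statistician | – |
| Principal and provider told | Study team | Yes, from then on; date relative to nomination not given |
| Referral strategy | Principal | Yes, if already told |
| Nomination | Teachers | Withheld until consent by one section; not concealed by another |
| First family contact | Typically the school provider | Yes, if already told |
| Consent and assent | Study team member | Yes (fully aware) |
| Caregiver and teacher baseline ratings | Caregivers, teachers | Release is tied to consent, not to baseline |

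The consent row does not depend on when the school is told. The HOPS program section also allows the school provider to be a general education teacher, the group that nominates, so one informed person could hold both roles.

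**2. Would the baseline significance screen catch an imbalance?**

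Inputs from the power paragraph: 20 HOPS and 10 TAU schools, 4.5 students per school, ICC 0.04. This gives 20 × 4.5 = 90 HOPS and 10 × 4.5 = 45 TAU/WL students. Assumed: a two-sided 0.05 test (no level is stated for baseline tests) and a true baseline gap of d SD.

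Power ≈ Φ(d/SE − 1.96), with SE = √(1/90 + 1/45) = 0.183. Allowing for clustering, the design effect is 1 + (4.5 − 1) × 0.04 = 1.14, so SE = 0.183 × √1.14 = 0.195.

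| d (assumed) | Flagged, no clustering | Flagged, ICC 0.04 |
|---|---|---|
| 0.2 | 19% | 18% |
| 0.3 | 38% | 34% |
| 0.5 | 78% | 73% |

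For HOPS-ST vs TAU/WL (45 vs 45, SE = √(2/45) = 0.211, no clustering), d = 0.3 is flagged about 30% of the time. A moderate gap would usually pass the screen.

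**3. What would a surviving bias do?**

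The stated MDES of 0.48 at 80% power and α = 0.025, with 28 degrees of freedom (30 schools − 2), implies SE = 0.48/(2.368 + 0.855) = 0.149. If a bias b remains in the adjusted estimate, the false-positive rate follows from a noncentral t with noncentrality b/0.149.

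| b (assumed, SD) | Type I error (nominal 0.025) |
|---|---|
| 0.1 | 0.06 |
| 0.2 | 0.17 |
| 0.3 | 0.38 |

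The values of d and b are assumptions; the documents supply none.

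**The case against.** The other side has substance.

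- **Timing at the school.** A reader might infer that all 135 students are recruited after the principal and provider know the arm. No sentence dates that disclosure relative to nomination, and the schedule and flow figures are not shown. What stands is that nothing delays disclosure and that consenting staff know the arm regardless.
- **Teachers and caregivers are shielded.** They nominate and decide, and eligibility uses the COSS-T interference items. This narrows the room for selection mainly to contact effort and the consent conversation. The shield is weakened by the Concealment section, and it does not cover the people who brief teachers and families.
- **Incentive.** It is tempting to infer that HOPS-school providers would pick easier students to limit their workload. At 4.5 students per school, split 1:1 between provider types, a school's provider side expects about two. TAU/WL students also receive HOPS later. The documents support no direction.
- **Size.** A reader might take an assumed 0.2–0.3 SD baseline gap, multiply by √0.60 = 0.775, and claim a bias of 0.155–0.232 SD, or 32–48% of the 0.48 MDES. That describes an unadjusted contrast. The plan includes covariates, and a baseline score that strong would remove most of the shift. Only selection on what is not measured would survive, and it has no number.
- **Contaminated baseline ratings.** These are possible, because release follows consent, but they are not stated to occur. Baseline grades come from the prior school year and so could not be altered this way.

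**Conclusion.** The concern holds as a possibility built into the design. Schools are randomised before students are recruited, consenting staff know the arm, and nothing in the protocol article keeps it from the principal and school provider while they run referral and family contact. The one safeguard is partial and conflicts with the Concealment section.

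Differential recruitment can affect both HOPS vs TAU/WL contrasts, with unknown size and direction; the documents do not show that it occurred. Adjustment for measured baseline scores would reduce it without removing it, and covariate selection by significance test is a weak defence at 90 vs 45 students. The percentages above rest on assumed imbalances and a 0.05 baseline test; the type I error figures also rest on the stated MDES.

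**What to change.** 1. **Reconcile** the student-assignment section with the Concealment section, so that the article says once who is told the assignment and when.
2. **For any school still recruiting**, keep the assignment with the statistician until the referred students have consented and caregiver and teacher baseline measures are complete. At the least, lock the list of nominated eligible students before disclosure. Change the release point for caregivers and teachers from consent to completed baseline.
3. **For students already enrolled**, prespecify adjustment for the baseline value of each outcome in every HOPS vs TAU/WL model, replacing covariate choice by significance test. Report nominated, eligible, approached and consented counts by arm, with dates of disclosure and baseline. Qualify the conclusion for possible recruitment bias, which the Discussion does not list among its limitations.

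**Cost.** Item 2 means schools learn their condition, and provider training starts, some weeks later. That is a real constraint for top-grade TAU/WL students, who are to receive HOPS before the school year ends. The stated enrolment window closed on 28/02/2026, before publication on 2026-06-11, so item 2 may apply to few schools or none, and item 3 is then the working remedy. Item 3 needs no new participants or visits, but the counts and dates must be recoverable from study records.
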